## Abstract

**Background:**

Declining intrinsic capacity (IC), encompassing domains such as locomotion, cognitive function, vitality, vision, hearing, and psychological well-being, is prevalent among older adults, impacting independence and quality of life (QoL). This study aims to develop and evaluate the Physiotherapy-led Person-Centered Integrated Care for Older People (PTICOPE) based on the WHO-ICOPE framework to enhance IC among older adults in Malaysia.

**Methods:**

This is a 12-week, multicenter, randomized controlled trial involving 70 community-dwelling older adults aged 60–75, recruited from three *Pusat Aktiviti Warga Emas* (PAWE) (Activity Center for Older Adults) in the Northern region of Malaysia. Participants will be randomized to either the intervention group, receiving the PTICOPE module workbook and guided use, or the control group, receiving general IC information, healthcare education, and self-care management. The recruitment of participants for this study has not yet commenced. Recruitment is expected to start after completing the validation of the PTICOPE module, however, it is anticipated that the recruitment start date is in February 2025 and will end in August 2025. Primary outcomes, including locomotor, psychological, cognitive, vitality, visual, and hearing functions using validated scales, will be collected at baseline, 4^th^, 8^th^, and 12^th^ week of the study period. Secondary outcomes will evaluate QoL, activities of daily living, urogenital health, and oral health at baseline and 12^th^ week. The normality of data will be checked. The independent t-tests, Chi-square tests, paired t-tests, and Repeated measures ANOVA will be used for data analysis, with a significant level at p < 0.05.

**Discussion:**

This study will develop a PTICOPE based on the WHO-ICOPE framework and test its efficacy in the older population residing in the community. The findings of this study hold the potential to establish an evidence-based approach for enhancing IC among community-dwelling older adults.

**Trials registration:**

Thai Clinical Trials (Number: TCTR20241029007).

## Introduction

Intrinsic capacity (IC) is a novel concept referring to the combination of an individual’s physical and mental abilities that define healthy and active aging, especially in later life [1,2]. The World Health Organization emphasizes that the well-being of older adults must be holistic, encompassing optimal functional capacity across six domains: locomotion, cognitive function, vitality, vision, hearing, and psychological function, which serve as biomarkers of healthy aging [3]. Older adults can achieve a higher quality of life (QoL) in their later years when they are in a supportive environment and reach the peak of each health domain, thereby reducing societal burdens [2]. However, as age advances, maintaining optimal IC becomes challenging due to natural aging processes, comorbidities, and healthcare services disruption [4,5].

Numerous studies have reported a high prevalence of IC decline, ranging from 49.9% to 84.5% [6–8]. A recent systematic review and meta-analysis indicated a pooled prevalence of IC decline of 67.8% within community settings (95% CI: 57.0-78.5%; p < 0.001) in which China had the lowest prevalence at 66.0% (95% CI: 53.2-78.9%), compared to 73.0% (95% CI: 59.8-86.3%) in other countries [1]. Another review and meta-analysis, using the WHO’s Integrated Care for Older People (ICOPE) screening tool, identified an overall IC impairment prevalence of 55.0%, with domain-specific prevalence rates as follows: locomotion (17.5%), cognition (18.2%), psychological well-being (12.1%), vitality (8.5%), vision (17.9%), and hearing (14.4%) [9]. Notably, the domains most and least affected by decline appear to differ by country. For instance, locomotion was reported as the most impacted domain in China, with psychological function least affected [10], while in India, locomotion was most impacted and vitality the least [8]. These variations may suggest the need for setting-specific, person-centered approaches and multidisciplinary care strategies to support older adults in the community considering differences in the sociodemographic factors, cultural norms, and local healthcare policy and infrastructure.

In response to the increasing global challenge of IC decline, the WHO launched the Integrated Care for Older People (ICOPE) framework in 2017, also known as WHO-ICOPE intending to provide a systematic approach to meeting the diverse health needs of older adults and to promote healthy aging within the community settings [11]. The framework consists mainly of the guidelines for a person-centered assessment process that guides the creation of individualized care plans informed by screening outcomes, followed by regular monitoring to assess effectiveness. The framework also has an additional emphasis on the value of involving community members and caregivers and encourages fostering connections with the broader environment and society. Several studies have applied the WHO-ICOPE framework to implement a person-centered care model for older adults. For instance, while the AMICOPE model provides a foundation, it has notable limitations, particularly its minimal focus on sensory domains [12]. Another approach, the INSPIRE-ICOPE program, was developed for older adults in affluent countries with generally higher education levels [13], which could reduce its applicability in culturally diverse settings such as Malaysia. Additionally, one study that used the ICOPE guidelines concentrated on a limited set of domains, specifically addressing cognitive, locomotor, and psychological aspects [14]. Given these limitations, further research is necessary to establish a more comprehensive, person-centered model that spans all IC domains, incorporating physical activity, personalized guidance, and routine follow-ups. Consequently, there is a need for healthcare providers to create robust, person-centered integrated care models that foster high functional capacity and improved well-being.

It is evident from previous studies that strategies for enhancing IC varied, which could be due to the researchers’ aim to target the specific needs of the study population. Due to that, interventions to enhance IC and functional abilities should be individualized, focusing on specific goals set by each individual, and can be delivered by any member of the multidisciplinary team. Furthermore, as Malaysia’s older population, particularly those in rural communities, may have limited access to comprehensive healthcare services, a person-centered approach that adapts and adopts the ICOPE framework could provide tailored interventions.

Findings indicate that locomotion is the most commonly affected domain [9], and that IC decline is independently associated with increased risks of frailty, disability, falls, fractures, and immobility [10], suggesting that physiotherapy plays a critical role in maintaining and enhancing IC among older adults. Therefore, we aimed to develop a Physiotherapy-led Person-Centered Integrated Care for Older People (PTICOPE) program and evaluate its effectiveness in improving IC among older adults living in the community. We hypothesized that older adults participating in the PTICOPE program would experience significant improvements in their IC domain scores, including mobility, vitality, psychological function, cognitive function, hearing, and vision, compared with the control group. This community-based program is expected to empower older adults to achieve greater independence, enhance their functional abilities, and improve their overall well-being. Additionally, it provides guidelines for physiotherapists and other healthcare professionals working with community-dwelling older adults to regularly screen IC and monitor outcomes effectively.

## Methods

### Study design

This study is a multicenter, randomized, parallel-group approach with a 1:1 allocation, randomly assigning participants to either the intervention or control group. The study is consistent with the guidelines of Standard Protocol Items: Recommendation for Trials (SPIRIT) (Fig 1). The protocol follows the CONSORT flowchart, outlining participant progression through the randomized controlled trial, with follow-ups scheduled at Weeks 4, 8, and 12 following the initial baseline assessment (Fig 2). Participants are informed of their assigned group. The recruitment of participants for this study has not yet commenced. Recruitment is expected to start after completing the validation of the PTICOPE module, however, it is anticipated that the recruitment start date is in February 2025 and will end in August 2025.

**Fig 1 pone.0318513.g001:**
[figure not shown]
SPRIT schedule for enrollment.

**Fig 2 pone.0318513.g002:**
[figure not shown]
The CONSORT flow diagram.

### Study settings

The study will be conducted at three community-based centers for older adults, also known as *Pusat Aktiviti Warga Emas* (PAWE), specifically in the districts of Sg Petani, Yan, and Kulim, Kedah, Malaysia. These centers were selected as they provide basic facilities that allow sufficient space for physical and social activities for community-dwelling older adults. Furthermore, these centers have a large number of registered older adults, around 200 to 300 members for each center, who have similar socioeconomic and cultural backgrounds.

### Participants

Community-dwelling older adults registered with PAWE will be invited to participate in the study. Most PAWE members are independent in activities of daily living and have controlled comorbidities. The inclusion criteria for participants are as follows: (1) aged 60 to 75 years; (2) able to walk independently or with partial assistance from an assistive device; (3) manageable comorbidities, as evidenced by their ability to participate in PAWE activities; (4) able to understand and communicate in either Bahasa Malaysia or English; and (5) willing to participate in the study. The exclusion criteria are: (1) uncontrolled comorbidities, such as hypertension, type 2 diabetes mellitus, cardiovascular disorders, or severe joint conditions; (2) Dementia or Alzheimer’s disease; and (3) blindness or deafness.

### Sample size determination

The sample size was calculated using G* Power 3 software for a repeated measures ANOVA (Baseline, week 4, week 8, week 12 measurements), aiming for a statistical power of 90%, an alpha level of 0.05, an estimated medium effect size (0.25), and a standard deviation of 2.5 for the primary outcomes and a correlation among repeated measures of 0.5. The selection of these parameters was guided by a previous study examining multicomponent exercise interventions in older adults to enhance, which reported a meaningful change of 1 point in the Short Physical Performance Battery (SPPB) as a clinically significant threshold [14].

Based on the initial analysis, a minimum of 60 participants is needed to detect a significant effect within each group. To account for potential attrition, such as participant dropouts due to withdrawal, health issues, or other factors, about 15 to 20% increase was applied. This adjustment results in a target sample size of 70 participants, divided equally into two groups (35 per group) to ensure the study maintains sufficient power to detect meaningful differences in IC changes between the intervention and control groups.

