### Outcome measures

#### Primary outcomes.

The repeated measures of the six domains of IC (cognitive decline, limited mobility [locomotor], malnutrition [Vitality], visual impairment, hearing loss, and depressive symptoms) are the primary outcomes of this study. These outcomes will be assessed at baseline and weeks 4, 8, and 12, using the WHO ICOPE screening tool. The ICOPE screening tool is a sensitive instrument to detect IC among community-dwelling older adults that does not require a substantial workforce [18]. It is used as the first step in each care pathway that covers all six core domains of IC to identify declines in IC across the six domains [19]. The psychometric properties of the ICOPE screening tools to assess IC domains among older persons from different settings have been reported in a few studies [20–22]. However, a systematic review found that the methods for assessing each of the IC domains differ substantially across studies and there is no consensus on the best method to compute an eventual global compound score to evaluate IC [23]. On the other hand, further improvements are needed in the vitality dimension of the ICOPE screening tool to enhance its sensitivity in identifying individuals at risk of malnutrition [24]. Hence, for this study, some measures of outcomes for the IC domains will be based on those validated in the Malaysian population.

We will use the validated Malay version of the Mini-Mental State Examination (MMSE) to measure cognitive function [25]. This tool includes items on orientation (5 points), registration (3 points), attention and calculation (5 points), recall (3 points), and language (9 points), with a maximum score of 30. A higher MMSE score indicates better cognitive function.

To assess locomotor or mobility function, we will use the Short Physical Performance Battery (SPPB) [26,27]. The SPPB comprises three components: gait speed (measured over 4 meters), lower limb strength (five-repetition chair rise), and static balance (side-by-side, semi-tandem, and tandem stands), with each component contributing up to 4 points. The total SPPB score ranges from 0 to 12, with higher scores indicating better locomotion.

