For vitality assessment in the ICOPE screening tool, we will use questions on unintended weight loss of more than 3 kg in the past three months and appetite loss. This study will employ the validated Malay version of the short-form Mini Nutritional Assessment (MNA) [28]. The MNA has a maximum score of 14, with higher scores indicating better nutritional status.

For hearing and vision assessments, we will follow previously reported procedures, using self-reported hearing and vision impairment [29]. Participants will be categorized as having total or severe loss (0 points), moderate loss (0.5 points), or normal to mild loss (1 point).

Psychological function, as indicated by depression level, will be assessed using the validated Malay short-form Geriatric Depression Scale (GDS-15) [30]. This scale consists of 15 items with “Yes” (1 point) and “No” (0 point) responses; a higher score indicates a greater level of depression.

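### The sample-size paragraph gives one SD of 2.5 for all primary outcomes, which is impossible for hearing and vision (maximum 0.5) and disagrees with the stated 1-point SPPB change and effect size of 0.25

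*Protocol article*

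**What the plan says.** Sample size determination describes a G*Power calculation "for a repeated measures ANOVA (Baseline, week 4, week 8, week 12 measurements", with 90% power, alpha 0.05 and a medium effect size of 0.25. The same sentence adds "a standard deviation of 2.5 for the primary outcomes and a correlation among repeated measures of 0.5". The choice of inputs is attributed to an earlier exercise study (reference 14) that reported "a meaningful change of 1 point in the Short Physical Performance Battery (SPPB) as a clinically significant threshold". The result is a minimum of 60, raised to 70 (35 per group) for attrition. The paragraph ends by saying that this keeps power adequate for between-group differences in IC change.

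Primary outcomes opens with "The repeated measures of the six domains of IC" and lists cognition, mobility, nutrition, vision, hearing and depressive symptoms. The instruments have different ranges: MMSE up to 30, SPPB 0 to 12, short-form MNA up to 14, and GDS-15 with 15 one-point items. For hearing and vision: "Participants will be categorized as having total or severe loss (0 points), moderate loss (0.5 points), or normal to mild loss (1 point".

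The Introduction describes reference 14 as a study that "concentrated on a limited set of domains, specifically addressing cognitive, locomotor, and psychological aspects [14".

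**The concern.** One SD cannot describe six outcomes on such different ranges, and for two of them the stated value is impossible. The anchor is a change on one instrument. One point is a modest step on the 12-point SPPB, but it is the whole scale for hearing or vision, and the exclusion criteria remove people who are blind or deaf. The description of reference 14 names neither vitality, hearing nor vision among the aspects it concentrated on.

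All six domains are primary, and the hypothesis in the Introduction names hearing and vision. A reader of the final report could therefore take a non-significant hearing or vision result as coming from a comparison that was powered to find an effect. The paragraph gives no basis for that.

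**Working it through.** **Inputs.** From Sample size determination: f = 0.25, alpha = 0.05, power 90%, m = 4 measurements, correlation 0.5, SD 2.5, 1 SPPB point, N = 60 before and 70 after attrition. From Primary outcomes: hearing and vision scored 0, 0.5 or 1. From the Introduction: pooled prevalences of 14.4% (hearing) and 17.9% (vision). Assumed here: sphericity and normal-theory tests.

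**1. The plan's own figure.** For the G*Power repeated measures ANOVA with two groups:
- Within-subject or group-by-time test: λ = N f² m / (1 − ρ) = N × 0.0625 × 4 / 0.5 = 0.5 N. 90% power needs a total N of 30; power is 99.8% at N = 60.
- Between-group main effect: λ = N f² m / (1 + (m − 1)ρ) = N × 0.25 / 2.5 = 0.1 N. 90% power needs N = 108; power is 67.3% at N = 60.

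The stated 60 is neither of these. It matches 2 × 30, that is, each arm sized alone for a change over time. The SD appears in neither formula, so replacing 2.5 by 0.5 changes neither N nor power.

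**2. The bound on the SD.** A variable confined to an interval has an SD of at most half the range: (1 − 0)/2 = 0.5. With the n − 1 divisor at n = 70 the limit is 0.5 × √(70/69) = 0.504. The stated 2.5 is 2.5/0.5 = 5 times the maximum.

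**3. Agreement of the inputs for SPPB.** If 2.5 is read as the SPPB SD, d = 1/2.5 = 0.40 and, for two equal groups, f = d/2 = 0.20. The stated f of 0.25 would mean a difference of 2 × 0.25 × 2.5 = 1.25 points. A single-visit two-sample t test at d = 0.40 has about 33% power with 30 per arm. If baselines are equal and the 1-point difference is present at weeks 4, 8 and 12, the group differences are (0, d, d, d), which gives an interaction f = d√3/8 = 0.40 × 0.2165 = 0.087. Then λ = 60 × 0.0075 × 8 = 3.6 and group-by-time power is about 32% (37% at N = 70).

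**4. Illustration for hearing and vision.** With a proportion p at 0.5 points and the rest at 1, the mean is 1 − 0.5p and the SD is 0.5√(p(1 − p)). In controls this is 0.175 (hearing) and 0.192 (vision). Let d be the mean difference divided by the root-mean-square of the two arm SDs. The effect is placed at weeks 4, 8 and 12 only, because randomization follows baseline. With ρ = 0.5, λ = N × 8 × (3/64) d², which is 22.5 d² at N = 60.

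| Outcome and scenario | Difference | d | Interaction f | Power, N = 60 | Power, N = 70 |
|---|---|---|---|---|---|
| Hearing, impairment halved | 0.036 | 0.23 | 0.05 | 13% | 15% |
| Vision, impairment halved | 0.045 | 0.26 | 0.06 | 16% | 18% |
| Hearing, impairment eliminated | 0.072 | 0.58 | 0.13 | 62% | 69% |
| Vision, impairment eliminated | 0.090 | 0.66 | 0.14 | 74% | 81% |

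**5. Range over prevalence.** If impairment is eliminated, d² = 2p/(1 − p). For 90% power at N = 60, λ must be about 14.5, so d = √(14.5/22.5) = 0.80 and p = d²/(2 + d²) = 0.24. For an interaction f of 0.25 itself, d = 0.25/0.2165 = 1.15 and p = 0.40. On this scoring, with complete elimination in the intervention arm, 90% power thus needs about 24% impaired in controls, and the planned f needs about 40%.

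**The case against.** A reader might infer that, because an SD of 2.5 is impossible for hearing and vision, the 90% power cannot hold for all six outcomes. The documents do not support that step. The named procedure runs on f = 0.25 and the SD plays no part in it. If f = 0.25 and ρ = 0.5 did hold for hearing or vision, nominal group-by-time power at N = 60 would exceed 90%. For a fixed raw difference, too large an SD understates power. Nor does the paragraph say that 90% holds for each outcome separately. All of this stands.

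It is also fair to object that the prevalences come from a pooled review and not from these centres, and that normal theory is rough for a three-level score. This stands too, so the table is illustrative only and does not show that an effect on hearing or vision could not be detected.

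Two further inferences should be avoided. Nothing says that 2.5 is the SPPB SD; only the 1-point change is tied to SPPB. And reference 14 is said to have concentrated on three aspects, which does not establish that it held no data on the others.

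What the objection does not remove is a stated input that is impossible for two primary outcomes, and a set of inputs that disagree even for the outcome they cite.

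**Conclusion.** The point holds in limited form. An SD of 2.5 cannot apply to hearing and vision, where the maximum is 0.5; this needs no outside data. The SD is redundant beside f = 0.25 and, taken with the 1-point SPPB change, implies f = 0.20. The paragraph therefore does not establish power for all six primary outcomes, and it does not say clearly which outcome was powered.

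It is not shown that power falls below 90% for hearing and vision. Under the stated assumptions (pooled prevalences, impaired participants at 0.5 points, effect at weeks 4, 8 and 12, ρ = 0.5, N = 60), group-by-time power is about 13% to 16% with impairment halved and 62% to 74% with it eliminated. Higher prevalence would raise these figures. The correction should be made before results are read, because it determines what a null result in these domains can mean.

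**What to change.** In Sample size determination:

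- Name the single outcome that the sample size refers to. SPPB is the natural choice, as the only instrument the paragraph cites.
- Delete the SD given for the primary outcomes collectively, or replace it with an SD for the named outcome that agrees with the 1-point difference and with f. Simply relabelling 2.5 as the SPPB SD and keeping 90% would not do, because 1/2.5 gives f = 0.20.
- Restate the power at the planned N for the group-by-time test from the reconciled inputs, with the assumed pattern of the effect over the visits.
- State that no power is claimed for the other five domains, hearing and vision in particular, that their results are reported as estimates with confidence intervals, and that a non-significant result is not read as absence of effect.

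The cost is a rewritten paragraph and a repeated calculation, with no extra participants or data. The downside is that the stated power will cover one domain instead of six and may be less favourable than 90%.

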### Randomization and allocation concealment

Participants will be randomly assigned to intervention and control groups using computer-generated randomization (http://www.randomizer.org/). A research assistant will handle the preparation of the envelopes by placing a carbon paper on top of the allocation paper, inserting both into a foil wrapper, and sealing them inside an envelope. Each envelope will be signed across the seal for authenticity. A total of 70 envelopes will be prepared with 35 allocated for the intervention group and 35 for the control group. Each envelope will be manually labelled as either “intervention” (1) or “control” (0). Once prepared, all 70 envelopes will be thoroughly shuffled to ensure randomness. A unique number sequentially from 1 to 70 will then be marked on the front of each envelope using a pen. The carbon paper inside will transfer this number onto the allocation paper. Finally, the envelopes will be placed in a plastic container in numerical order and ready to be used for the group allocation. After recruiting a participant, the research assistant will sequentially open an envelope, with the number inside indicating the participant’s group assignment. In this study, neither the participants nor the research assistants will be blinded to group assignments; however, the data collector will be blinded to group assignments to minimize measurement bias.

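### The allocation procedure contradicts itself on where the sequence comes from and whether the arm is visible on the envelope, and it does not ensure balance within centres

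*Protocol article*

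**What the plan says.** All quotations are from the protocol article, section Randomization and allocation concealment. It opens with "Participants will be randomly assigned to intervention and control groups using computer-generated randomization", using a web randomizer. It then sets out these steps, in this order:

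1. A research assistant puts carbon paper and an allocation paper into foil, seals them in an envelope and signs across the seal.
2. "A total of 70 envelopes will be prepared with 35 allocated for the intervention group and 35 for the control group".
3. "Each envelope will be manually labelled as either “intervention” (1) or “control” (0").
4. "Once prepared, all 70 envelopes will be thoroughly shuffled to ensure randomness".
5. "A unique number sequentially from 1 to 70 will then be marked on the front of each envelope using a pen", and the carbon copies that number onto the allocation paper.
6. "the envelopes will be placed in a plastic container in numerical order and ready to be used for the group allocation".
7. "After recruiting a participant, the research assistant will sequentially open an envelope", and the number found inside gives the group.

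Other sections supply the context. Study design gives a 1:1 ratio and says recruitment had not begun. Study settings names three centres. Data collection and monitoring places assignment after baseline measurement and has research assistants help deliver the intervention. Ethics and dissemination has research assistants meet potential participants and explain the study.

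**The concern.** Two features protect a randomized comparison at entry: an unpredictable sequence, and concealment of the next assignment until the participant is committed. The section leaves the first without a clear source and describes the second in a way that could undo it.

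If the person enrolling can see the next arm, they can bring forward, delay or discourage a volunteer according to fitness or keenness. The eligibility criteria leave room for this, since manageable comorbidity and willingness to take part are matters of judgement. Measuring baseline before assignment does not help if the arm can be read beforehand. Selection of this kind cannot be reliably repaired in the analysis. Participants know their group and hearing and vision are self-reported, so much of the trial's credibility rests on allocation.

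Centre balance is a lesser matter. It affects precision and the face validity of the baseline table, not bias.

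**Working it through.** **1. The plan's own figure.** 35 + 35 = 70 envelopes. This agrees with the 1:1 ratio and with the target sample size of 70. If every envelope is used, overall balance is exact.

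**2. Where the sequence comes from.** Envelopes are used in numerical order, so the order in which numbers are written on them is the allocation sequence. Numbers are written after the shuffle, so the shuffle creates the sequence. None of the seven steps takes an input from the web randomizer. The opening sentence and the procedure therefore describe two different methods. This holds wherever the arm label is placed.

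**3. Where the arm can be seen.**

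| Statement | Implies |
|---|---|
| The envelope is the object labelled 1 or 0, in the text after sealing and signing | Arm on the outside, readable before use |
| Foil, seal, signature across the seal | Arm meant to be hidden |
| The number inside gives the group | Arm on the inner paper |
| Carbon copies the 1 to 70 number onto the inner paper | The number inside could also be the envelope number |

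The first row conflicts with the next two. The fourth makes the third ambiguous.

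**4. What is at stake in predictability.** With the arm readable outside, the next assignment is known 100% of the time. With it hidden, someone who knows every past assignment and always guesses the arm with more envelopes left is right about 57% of the time (simulation of a 35/35 list), against 50% by chance. The location of the label is what matters; the fixed 35/35 total is minor.

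**5. Balance within centres.** Recruits per centre are not stated, so the splits below are assumptions. For a centre with n recruits drawn from one shuffled 35/35 list, the number X in the intervention arm is hypergeometric (70, 35, n). The arm difference is D = 2X − n, and Var(X) = n × ½ × ½ × (70 − n)/69.

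- n = 24: Var(X) = 24 × 0.25 × 46/69 = 4.0, so SD(D) = 2 × 2.0 = 4.0. Exact mean |D| = 3.1 and P(|D| ≥ 6) = 0.208.
- n = 23: Var(X) = 23 × 0.25 × 47/69 = 3.92, so SD(D) = 2 × 1.98 = 3.96. Exact mean |D| = 3.2 and P(|D| ≥ 7) = 0.126. D is odd here, so 6 or more means 7 or more.

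For the worst of three centres, sum C(n₁,x) C(n₂,y) C(n₃,35−x−y) / C(70,35) over all outcomes in which any centre reaches the threshold:

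| Assumed split | P(worst centre ≥ 6) | P(worst centre ≥ 7) |
|---|---|---|
| 24/23/23 | 0.329 | 0.247 |
| 35/20/15 | 0.299 | 0.223 |
| 30/20/20 | 0.401 | 0.168 |

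Under 24/23/23 the worst centre differs by 4.8 on average. With a separate list per centre in blocks of 4 (an illustrative size), the difference within a centre could never exceed 2.

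**The case against.** The strongest reply is that the label was meant for the allocation paper. Foil, a signed seal and an assignment read from inside make no sense if the arm is on the outside, and the codes 1 and 0 fit a number found inside. This is a fair reading and may well be what was intended. For that reason the stronger inference a reader might draw, that the next allocation is certainly exposed and the safeguards conceal nothing, is not supported. What remains is that the sentence names the envelope as the thing labelled, and a procedure must be safe when followed as worded.

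Second, a thorough shuffle of sealed envelopes is still a random process. That stands: no bias is shown from shuffling itself. But it cannot be reproduced or audited, and it is not the method the section claims.

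Third, a reader might infer that the single series leaves the arms unbalanced by centre. It does not do so by necessity. Under the near-equal split, about two times in three no centre differs by 6 or more. Chance imbalance is not bias, and the protocol describes centre members as similar in background. An article may also omit stratification, although one numbered series in one container argues against it.

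Fourth, the article assigns tasks to research assistants as a role. It does not say that the same individual recruits, prepares and opens envelopes, and helps deliver the intervention. Equally, it states no separation of those tasks.

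**Conclusion.** The point holds as an internal contradiction in a stated procedure, not as missing detail. Two parts are firm: the computer-generated sequence is announced but never used, and the section conflicts with itself on whether the arm is on the outside of the envelope. The consequence is conditional: if staff follow the literal wording, all 70 allocations can be known before enrolment; if the label is inside, predictability is about 57%.

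The centre point is secondary and should be put as a failure to ensure balance. The chance that at least one centre differs by 6 or more is about 33% for 23/23/24, and 30% to 40% across the three assumed splits.

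This should be corrected before the first participant is enrolled, because selection at entry cannot be dependably undone later.

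**What to change.** Rewrite the section so that one procedure is described from start to finish:

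- State that the arm appears only on the slip inside the opaque sealed envelope, and that nothing outside identifies it.
- Delete the shuffle. Fill the numbered envelopes in the order of the computer-generated list, and keep that list as the audit record.
- Preferably use one list per centre, with randomly varying block sizes.
- Have an existing team member who neither recruits nor assesses hold the list and fill the envelopes.
- Write the participant ID and date on the sealed envelope before it is opened. Keep assignment after baseline, as the protocol already has it.

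The cost is a change of wording, about an hour to generate the lists and fill the envelopes, and slightly more complex logistics from holding three sets instead of one. No extra staff are needed. Small blocks bring some predictability at block ends, which varying the sizes reduces but does not remove.
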